#### Other measures

Development and Well-being Assessment (DAWBA^29^): The DAWBA is a semistructured, investigator-based diagnostic interview for child mental health problems, including ADHD, which includes the (Strengths and Difficulties Questionnaire; SDQ^30^) as an initial screen. The parent and teacher DAWBA will be completed to compare the accuracy of clinic diagnosis (in QbO and QbB arms of the trial) to that of an independent clinical consensus diagnosis made using the DAWBA. Two experienced clinicians, blind to allocation, will review the DAWBA and arrive at a clinical consensus diagnosis.QbTest scores: Q-scores for attention, impulsivity and activity will be compared with DAWBA ADHD diagnosis to obtain the best predictive model based on QbTest scores that discriminates between ADHD ‘positive’ and ADHD ‘negative’ gold standard DAWBA diagnosis.Side-effects scale:^31^ Side-effects scale will be completed as a control check in medicated participants to ensure greater speed to diagnosis/medication normalisation is not off-set by greater side effects.SNAP-IV:^32^ The proportion of patients achieving symptom normalisation assessed via the SNAP-IV. If the young person receives a QbTest on medication (Qb2), the timing on the 3-month SNAP-IV will be moved to coincide with Qb2 to provide a direct comparison of subjective (SNAP-IV) and objective (QbTest) measures. The SNAP-IV is a rating scale designed to assess ADHD symptoms.SDQ:^30^ The SDQ is a brief behavioural screening questionnaire which can be used as part of a clinical assessment.C-GAS (Children's Global Assessment Scale^33^): Clinician opinion of patient outcome will be assessed via the C-GAS. The C-GAS is a 0–100 scale which that integrates psychological, social and academic functioning in children.EQ-5D-Y (EuroQol Five Dimensions Heath Questionnaire-Youth^34^): Child health-related quality of life will be assessed using the EQ-5D-Y.A resource collection profile tool will be used. It will encompass elements of a CSRI (Client Service Receipt Inventory^35^) often used in mental health studies but will be a specifically designed economic collection pro-forma for the purpose of this study. It will collect demographic details as well as information on all the services used by the child and family borne costs to be estimated. Indirect costs such as time lost from work incurred by the child's parents or carers will further be recorded. This measure will enable a societal wide perspective for a cost-effectiveness analysis of the QbTest. The DAWBA^29^ QbTest^22^ SDQ^30^ Side-effects scale,^31^ SNAP-IV^32^ C-GAS^33^ EQ-5D-Y^34^ and CSRI^35^ all have established reliability, validity and history of use in clinical and research settings.

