**Figure 1 BMJOPEN2014006838F1:**
[figure not shown]
Study flow chart. ADHD, attention deficit/hyperactivity disorder; CAMHS, Child and Adolescent Mental Health Services.

Phase 1, Assessment: The first phase investigates the use of QbTest as a tool to aid diagnosis. Participants will undergo ADHD ‘assessment as usual’, which varies between clinics, clinicians and cases, but will typically involve an interview with the parent/young person and collection of questionnaires from the parent/young person and teacher. While attending the clinic, the participant will be asked to complete the QbTest at some point during the diagnostic process. Participants will also be asked to complete baseline outcome measures (see measures section).

Phase 2, Treatment: Patients who receive a clinic diagnosis of ADHD and are allocated by clinicians to receive ADHD medication initiated within 3 months of their baseline assessment will be asked to complete a second QbTest (Qb2) 4–8 weeks after medication initiation. This timeframe was chosen to ensure that all participants can complete their second QbTest before the 6-month follow-up.

All participants will stay in the trial for 6 months and will be asked to complete outcome measures at 3 and 6-month follow-up, regardless of their diagnosis or whether they receive medication. With the aim of promoting participant retention and completion of follow-up measures, participants will be compensated for their time with a £15 high-street voucher if they remain in the trial until 6 months.

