### Data analysis plan

The analysis will be conducted on an intention-to-treat (ITT) basis. Exploratory analysis will be conducted first for outcome and patient background variables; descriptive statistics of each variable will be presented separately for each group at each follow-up point, with means and SD for normally distributed variables, medians (IQR) for skewed variables and frequency (percentage) for categorical variables. Missing values will be checked and reported. Multiple imputation will be used to hand missing values, based on a multilevel modelling approach.

To compare the number of visits needed to achieve an ADHD diagnosis (either confirmed or excluded) between groups, Poisson regression with binary group status as the explanatory variable will be implemented. To compare clinician's confidence in their diagnostic decisions, multilevel modelling with patient as a level 2 unit will be used to take into account the non-independence within patient data due to repeated measures.^41^

κ Statistics will be used to reflect the stability of diagnosis between first confirmed diagnosis and diagnosis rerated at 6-month follow-up time. κ Statistics will be reported for each group and the stability of diagnosis will be compared between arms using logistic regression. The same analysis approach will be implemented to explore the stability of diagnosis confidence between time of first confirmed diagnosis and 6-month follow-up. To assess the diagnosis accuracy, the sensitivity, specificity, likelihood ratio (LR) ve+, LR ve−, positive predictive value (PPV) and negative predictive value (NPV) will be reported for each group and the test performance will be compared between QbO and QbB arms.^42^
^43^ Receiver operating characteristic curve analyses will be used to obtain the best predictive model based on QbTest scores that discriminates between ADHD ‘positive’ and ADHD ‘negative’ gold standard DAWBA diagnoses.

For treatment related outcomes (phase 2) outcome measures such as SNAP-IV, side effects scale, SDQ and C-GAS scores, multilevel modelling with patient as a level 2 unit will be again applied to quantify the difference between QbO and QbB arms.

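### The side-effect check compares the arms only among medicated children, so it cannot show extra side effects that arise because more children are medicated

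*Protocol article*

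**What the plan says.** Under Other measures, the article fixes both who completes the scale and why. The scale is to be "completed as a control check in medicated participants to ensure greater speed to diagnosis/medication normalisation is not off-set by greater side effects".

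The Data analysis plan groups the scale with other measures: "For treatment related outcomes (phase 2) outcome measures such as SNAP-IV, side effects scale, SDQ and C-GAS scores". For these, "multilevel modelling with patient as a level 2 unit will be again applied to quantify the difference between QbO and QbB arms".

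Trial phases describes phase 2 as children with a clinic diagnosis of ADHD who are "allocated by clinicians to receive ADHD medication initiated within 3 months of their baseline assessment". The same section has every participant followed at 3 and 6 months, whatever the diagnosis or treatment.

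The Data analysis plan opens with a general rule: "The analysis will be conducted on an intention-to-treat (ITT) basis". It also plans multiple imputation for missing values. It gives no rule for the side-effects scale in children who are never medicated. The body of Table 1, which may say more about who completes which form and when, is not available in the text reviewed.

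**The concern.** The check is meant to weigh faster diagnosis and normalisation against side effects. The benefit side (visits and days to diagnosis) is compared between the randomised arms. The harm side is compared only among children who went on to be medicated.

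If seeing the report changes who is medicated, or when, two things follow. The medicated groups are no longer balanced by randomisation. And the comparison holds fixed the route by which a test report could cause side effects, namely the child being put on medication. The average medicated child could fare equally well in both arms while more of the assessed children had side effects. The result would then read as reassurance in the direction that favours the test.

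**Working it through.** **Figures in the plan.** The side-effect check has no figure of its own. The sample size matters here only for precision, so I checked it first. The inputs from Sample size and justification are Poisson means of 2.94 and 2.18, 80% power and two-sided 0.05. On the log rate ratio scale:

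n per arm = (1.960 + 0.842)² × (1/2.94 + 1/2.18) / [ln(2.94/2.18)]² = 70.09, so 71. Then 142/0.8 = 177.5, so 178.

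Both agree with the article. The stated maximum of 234 is 117 per arm recruited. I use 71 per arm (evaluable, at the minimum) and 117 per arm (recruited, at the maximum) as the range.

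**More children medicated.** Let m be the proportion medicated in an arm and s the proportion of medicated children with a side effect. The medicated-only comparison looks at s. The rate per randomised child is m × s. The article gives neither m nor s, so all values are assumptions.

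| Assumed m, QbBlind v QbOpen | s, both arms | Medicated-only difference | Per randomised child |
|---|---|---|---|
| 50% v 60% | 40% | 0 | 0.50 × 0.40 = 20% v 0.60 × 0.40 = 24% |
| 50% v 65% | 40% | 0 | 20% v 0.65 × 0.40 = 26% |
| 40% v 60% | 40% | 0 | 16% v 24% |

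The first two rows are relative increases of 20% and 30%. Over a wider grid (30 v 40%, 40 v 50%, 40 v 60% and 50 v 65% medicated; s from 20% to 60%), the difference per randomised child runs from 2 to 12 percentage points. The medicated-only difference is 0 throughout.

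**The sign can reverse.** Take 40% v 60% medicated, and suppose the extra 20% medicated in QbOpen have a side-effect rate of 20% against 40% in the rest. The QbOpen rate per medicated child is (0.40 × 0.40 + 0.20 × 0.20)/0.60 = 0.20/0.60 = 33%, against 40% in QbBlind. Per randomised child it is 20% against 16%. The check would favour QbOpen although more QbOpen children were affected.

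**Earlier medication.** The answer depends on what the scale records. Suppose it captures any side effect since starting, with a constant monthly hazard h and 4 v 3 months on medication by month 6. The proportion affected among the medicated is 1 − exp(−h × t):

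- h = 0.1: 33% v 26%
- h = 0.2: 55% v 45%

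The medicated-only comparison then points the right way, though with 36 medicated per arm (about half of 71) power is only about 10% to 13%. If the scale records current side effects at a stable rate, the difference is 0 and the longer exposure is not seen.

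**Precision of an all-randomised comparison.** For 20% v 26%, the 95% half-width is 1.96 × √[(0.20 × 0.80 + 0.26 × 0.74)/n]. This is about 14 points at n = 71 and 11 points at n = 117, around a difference of 6 points. Across the grid, power is about 6% to 34% at 71 per arm and 8% to 52% at 117 per arm.

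**The case against.** The best defence is that the scale has a narrower job. Half of the stated purpose concerns medication normalisation, which the Introduction ties to titration. For the question of whether better titration costs tolerability, treated children are a natural population. That stands, and it is a reason to keep the medicated-only score. It does not cover the other half of the sentence, on speed to diagnosis.

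Three stronger readings are tempting, and the article does not support them.

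- **That this is the only protection against harm.** Data monitoring has adverse events recorded without restriction to medicated children. SDQ and C-GAS are compared by arm. Over-diagnosis, one route to unwarranted medication, is addressed by comparing diagnostic accuracy between arms against a blinded DAWBA consensus. What can be said is narrower: it is the only between-arm comparison of side effects stated, because no comparison by arm is given for adverse events.
- **That harm from earlier medication cannot be seen.** As the working shows, it can be, if the scale is cumulative.
- **That QbTest will medicate more children.** The article expects shorter delays, and it cites a study in which the test reduced missed ADHD. It does not predict a higher proportion medicated. Faster diagnosis could raise the number medicated within the fixed 3- and 6-month windows, but by how much is unknown.

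It is also fair that an all-randomised rate counts expected side effects of warranted treatment, so it has to be read beside benefit. The handling of children who stop medication may be settled in documents not shown. The general intention-to-treat statement does not resolve the main point: a scale that unmedicated children do not complete needs a stated rule for them, and imputing side-effect scores for them would make little sense.

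**Conclusion.** The point holds in limited form. As stated, the side-effect comparison conditions on a post-randomisation event that the report may influence. It is not protected by randomisation, and it cannot show extra side effects that arise because more children are medicated within follow-up. It may or may not show those from earlier medication, depending on whether the scale captures current or cumulative effects.

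No stated figure is wrong, and the size of the problem cannot be derived from the article. The contrast of 0 against 20% v 24-26% rests entirely on assumed medication and side-effect rates. If equal proportions were medicated with equal rates, both denominators would show no difference. The weakness lies in the stated comparison and not in the data, since the clinician pro-forma already records medication at each consultation. It is worth correcting before analysis, chiefly to avoid reading a null medicated-only result as evidence that faster diagnosis carries no side-effect cost.

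**What to change.** Keep the medicated-only score and label it a description of tolerability among treated children. Beside it:

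1. Add a comparison over all randomised children of the proportion with a medication side effect by 6 months. Count never-medicated children as having none instead of imputing scores. Include children who started and then stopped, using their last completed scale.
2. Report by arm the proportion medicated and the time on medication.
3. State whether the scale is scored as current or cumulative side effects.
4. Present the result as an estimate with a confidence interval, read beside benefit and diagnostic accuracy, and say that a non-significant result would not show safety.

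The cost is mainly analysis wording, because medication is already on the pro-forma and all participants are followed to 6 months. The downsides are low precision at 71 to 117 per arm and the need for an agreed rule, and a completed scale, for children who stopped.

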
#### Feasibility and acceptability

QbTest opinion questionnaire and interview: Clinician and patient opinion of the QbTest will be assessed via a questionnaire, developed by [name] and currently used to assess QbTest opinion in on-going studies at the Queens Medical Centre, Nottingham. This will provide information on the acceptability of QbTest in routine NHS settings. A subsample (n=20) of families and clinicians will be invited to participate in qualitative interviews to further explore acceptability and feasibility of the QbTest. The subsample will be chosen at random from each participating site, using a random number generator.

Table 1 displays a summary of measures, the informant and the time point of completion. All measures will have a 1-month window for completion, with the exception of the clinic pro-forma which must be completed during or just after the clinic appointment and the QbTest which must form part of the diagnostic or medication assessment. The collected outcome measures for participants who drop out the trial before 6 months will be included in analysis, no further outcome measures will be collected from these participants after they terminate their participation.

**Table 1 BMJOPEN2014006838TB1:** Synoptic table of study measures

[figure not shown]

*If ADHD diagnosis record and medicated within 3 months of baseline assessment (in place of corresponding 3 month assessment in grey).

†Completed at every appointment.

C, clinician completed; P, parent/carer completed; T, teacher completed.

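### The 3-month SNAP-IV is moved for early-medicated participants only, so its timing may differ by arm, and the population for the phase 2 comparisons is ambiguous

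*Protocol article*

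**What the plan says.** Under Trial phases (text after Figure 1), phase 2 covers patients with a clinic diagnosis of ADHD who are "allocated by clinicians to receive ADHD medication initiated within 3 months of their baseline assessment". They "will be asked to complete a second QbTest (Qb2) 4–8 weeks after medication initiation".

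Under Other measures, if that second test takes place, "the timing on the 3-month SNAP-IV will be moved to coincide with Qb2". The stated purpose is a direct comparison of the subjective and the objective measure. The footnote to Table 1 describes the same substitution: "If ADHD diagnosis record and medicated within 3 months of baseline assessment (in place of corresponding 3 month assessment in grey". The table itself is not shown, so which measures besides SNAP-IV are replaced cannot be checked. The text above the table adds that "All measures will have a 1-month window for completion", but exempts the QbTest from that window.

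The Data analysis plan opens with "The analysis will be conducted on an intention-to-treat (ITT) basis". It later applies a multilevel model, with patient as the level 2 unit, to quantify the difference between arms "For treatment related outcomes (phase 2) outcome measures such as SNAP-IV, side effects scale, SDQ and C-GAS scores". Normalisation is compared by logistic regression at 6 months.

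Trial phases also says that all participants "will be asked to complete outcome measures at 3 and 6-month follow-up, regardless of their diagnosis or whether they receive medication". The side-effects scale is the exception: Other measures has it completed by medicated participants, as a control check.

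**The concern.** Whether a participant's 3-month SNAP-IV is moved, and to what date, depends on three events after randomisation: a diagnosis of ADHD, a decision to medicate, and a start within 3 months. The trial's main hypothesis is that QbTest brings the first of these forward. If it does, the share of moved scores and their dates will differ between arms.

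The rule also changes the clock, from time since baseline to time since starting medication. A child who starts at week 0 would have had 13 weeks on medication at the fixed visit but has 4–8 weeks at the moved one. A child who starts at week 13 would have had none but also has 4–8 weeks. Any advantage of earlier treatment at a common calendar time is partly removed. A model with a single 3-month category would read the result as a difference in symptoms at one time.

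A second question is who enters the phase 2 model. If the phase 2 label is read as Trial phases defines it, SNAP-IV, SDQ and C-GAS would be compared in groups formed after randomisation.

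**Working it through.** **The plan's own figure.** The article gives no figure for this comparison. The audit means used below (2.94 and 2.18 visits, from Sample size and justification) do reproduce its sample size:

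n = (1.960 + 0.842)² × (1/2.94 + 1/2.18) / [ln(2.94/2.18)]² = 70.09, so 71 per group; 142/0.8 = 177.5, so 178 in total.

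That calculation is not in question here.

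**Range of the moved score, from the protocol's own windows.** One month is 52.18/12 = 4.35 weeks.

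- Fixed 3-month visit: 3 × 4.35 = about week 13.
- Fixed visit with the 1-month window read as plus or minus one month (an assumption): about weeks 8.7 to 17.4.
- Moved score, earliest: 0 + 4 = week 4.
- Moved score, latest: 13 + 8 = week 21.
- 6-month visit: 6 × 4.35 = about week 26. The latest moved score precedes it, as the article intends.

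**Possible difference between arms (illustration only).** Assumptions not in the document: visits = 1 + Poisson(mean − 1) at the audit means; first visit at week 0; equal spacing of 3 to 6 weeks; medication starts on the day of decision; second QbTest 6 weeks later. Write p for the share reaching a decision by week 13 and t for the mean week of the moved score among them.

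Worked example at 6-week spacing, where up to 2 further visits fit in 13 weeks:

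- QbBlind: p = e^(−1.94) × (1 + 1.94 + 1.94²/2) = 0.69; mean further visits given at most 2 = 1.18; t = 6 × 1.18 + 6 = 13.1.
- QbOpen: p = e^(−1.18) × (1 + 1.18 + 1.18²/2) = 0.88; mean further visits = 0.89; t = 6 × 0.89 + 6 = 11.4.

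| Spacing (weeks) | p, QbBlind | t, QbBlind | p, QbOpen | t, QbOpen | Difference in t |
|---|---|---|---|---|---|
| 3 | 0.952 | 11.3 | 0.993 | 9.5 | 1.8 |
| 4 | 0.868 | 12.2 | 0.968 | 10.3 | 1.9 |
| 5 | 0.693 | 11.9 | 0.884 | 10.5 | 1.4 |
| 6 | 0.692 | 13.1 | 0.884 | 11.4 | 1.7 |

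The p values count any decision. They are not phase 2 entry rates, because some decisions exclude ADHD and some diagnosed children are not medicated. If a fraction f of decisions, equal in both arms, leads to medication, the mean week over all participants is 13 − f × p × (13 − t). At 6-week spacing this is 13 + 0.07f in QbBlind and 13 − 1.44f in QbOpen, a difference of 1.5f weeks. Over the four spacings the difference is 1.5f to 1.9f weeks, or about 0.7 to 1.0 week at f = 0.5.

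**Selection, if the model were restricted to early-medicated patients (illustration only).** Let a standard normal trait U, such as severity, shorten the path to a decision: visits = 1 + Poisson[(mean − 1) × exp(−bU − b²/2)], with b = 0.2 or 0.4 and spacing of 4 or 6 weeks, all assumed. The selected groups then differ between arms in mean U by 0.06 to 0.15 SD. If QbTest does not change speed, this route produces no expected imbalance.

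**The case against.** The strongest reply is that all participants are followed at 3 and 6 months whatever their diagnosis or treatment, and that the analysis is by intention to treat. Nothing restricts SNAP-IV, SDQ or C-GAS to medicated children, and the phase 2 label may be no more than a topic heading. This largely stands. A reader might infer that those scales are compared only in selected patients, but the document does not say so. What remains is an ambiguity between that label, the definition of phase 2, and the intention-to-treat statement. It does not extend to the side-effects scale, which is collected in medicated participants and yet listed in the same between-arm model.

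A reader might also infer that the normalisation aim carries the timing bias. It does not: that proportion is compared at 6 months, and that visit is not moved.

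It can also be said that coding of time in a multilevel model belongs in an analysis plan that is not shown, and that the substitution is deliberate and declared. Both are fair. The article does not say that time will be coded as a single category, and the wide range is not a breach of the window. But the replacement is a rule of data collection. Where the moved score takes the place of the 3-month score, no later analysis plan can recover a score at the fixed date.

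Finally, weeks 4 to 21 is a range across patients. The mean difference between arms is much smaller and arises only if QbTest alters the speed of diagnosis or medication. That stands.

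**Conclusion.** The concern holds in limited form. The date of the 3-month SNAP-IV depends on an event after randomisation that the intervention is expected to affect. The range of about 4 to 21 weeks, against about week 13 for everyone else, follows from the protocol's own windows. The arms may therefore differ in timing, and a model that treats the score as one time point may be biased. The size of the arm difference rests on the assumptions shown: 1.4 to 1.9 weeks among moved scores, and less over all participants when only some are medicated. The effect on SNAP-IV points cannot be derived from the document.

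The side-effects comparison is made in a group formed after randomisation. For SNAP-IV, SDQ and C-GAS the population is ambiguous, not shown to be restricted. The primary outcome and 6-month normalisation are unaffected by the moved visit. The point deserves correction but does not threaten the trial's main result.

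**What to change.** In the Data analysis plan:

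- State that the between-arm effects on SNAP-IV, SDQ, C-GAS and normalisation are estimated in all randomised participants at the fixed 6-month visit.
- If the earlier SNAP-IV enters a longitudinal model, enter it at actual days since baseline. Otherwise reserve the score matched to the second QbTest for the subjective–objective comparison, which is the reason given for moving it.
- Label all medicated-only comparisons, including side effects, as descriptive and non-randomised.

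The cost is wording only; every participant is already due a 6-month assessment and no visit changes. The downside is that unmedicated participants dilute any effect that acts through medication, but what is estimated is the randomised effect. Actual days reduce the timing problem without fully removing it, because the date of measurement still depends on diagnosis and treatment. The 6-month comparison should therefore carry the conclusion.
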